## Abstract

**Background:**

Increasing evidence suggests the bidirectional interplay between parathyroid hormone and aldosterone as an important mechanism behind the increased risk of cardiovascular damage and bone disease observed in primary hyperparathyroidism. Our primary object is to assess the efficacy of the mineralocorticoid receptor-blocker eplerenone to reduce parathyroid hormone secretion in patients with parathyroid hormone excess.

**Methods/design:**

Overall, 110 adult male and female patients with primary hyperparathyroidism will be randomly assigned to eplerenone (25 mg once daily for 4 weeks and 4 weeks with 50 mg once daily after dose titration] or placebo, over eight weeks. Each participant will undergo detailed clinical assessment, including anthropometric evaluation, 24-h ambulatory arterial blood pressure monitoring, echocardiography, kidney function and detailed laboratory determination of biomarkers of bone metabolism and cardiovascular disease.

The study comprises the following exploratory endpoints: mean change from baseline to week eight in (1) parathyroid hormone(1–84) as the primary endpoint and (2) 24-h systolic and diastolic ambulatory blood pressure levels, NT-pro-BNP, biomarkers of bone metabolism, 24-h urinary protein/albumin excretion and echocardiographic parameters reflecting systolic and diastolic function as well as cardiac dimensions, as secondary endpoints.

**Discussion:**

In view of the reciprocal interaction between aldosterone and parathyroid hormone and the potentially ensuing target organ damage, the EPATH trial is designed to determine whether eplerenone, compared to placebo, will effectively impact on parathyroid hormone secretion and improve cardiovascular, renal and bone health in patients with primary hyperparathyroidism.

**Trial registration:**

ISRCTN33941607

## Background

Parathyroid hormone (PTH) is synthesized and secreted in the chief cells in the parathyroid gland mainly in response to a decreased circulating ionized calcium concentration. PTH regulates the calcium und phosphate homeostasis by activating osteoclasts and osteoblasts, enhancing intestinal Ca^2+^ absorption, promoting the synthesis of active vitamin D in the kidney and increasing active renal Ca^2+^ reabsorption. Elevation of plasma Ca^2+^ concentration in turn decreases PTH secretion by activating calcium sensing receptors located on chief cells. A well-balanced calcium homeostasis is crucial for the regulation of cell signalling, neuromuscular function and bone metabolism.

Primary hyperparathyroidism (PHPT), the third most common endocrine disorder, is characterized by excess PTH secretion, inappropriate with respect to the prevailing circulating ionized calcium concentration
[1]. The identification of PTH receptors within the cardiovascular (CV) system e.g. in cardiomyocytes, vascular smooth-muscle and endothelial cells, indicates that PTH excess may have a potential impact on CV health. In fact, various observational studies linked PTH excess to a higher risk of hypertension, left-ventricular hypertrophy, arrhythmia and metabolic disorders
[2-4].

Several observational studies in humans point to an eminent role of the mineralocorticoid hormone aldosterone, produced within the zona glomerulosa (ZG) of the adrenal gland, in the pathogenesis of CV and renal disease
[5-7]. Relative excess of aldosterone may play an important role in the genesis of CV damage even in the absence of primary aldosteronism
[8].

Accumulating evidence points to the bidirectional interplay between PTH and aldosterone as an important mechanism behind the increased risk of CV damage observed in PHPT
[9,10]. Experimental and clinical data support the notion that PTH directly stimulates adrenal steroid secretion by inducing calcium entry in adrenal ZG cells via binding to PTH/PTH-related protein receptor (PTH/PTHrP receptor = PTH1R), voltage-gated L-type calcium channels and by activating various signal transduction pathways
[11,12]. The resulting relative aldosterone excess triggers increased PTH secretion by facilitating renal and fecal calcium loss, which in turn aggravates PTH secretion and CV damage
[13].

Given the linkage between aldosterone and PTH, treatment of either disease (primary aldosteronism and PHPT) results in positive effects in the other hormone system. However, studies evaluating the effects of mineralocorticoid receptor (MR)-blockade on PTH secretion, CV health and bone metabolism in patients with PHPT are missing. We therefore suggested the working hypothesis that in patients with PHPT MR-blockade with eplerenone decreases iPTH(1–84) levels and exerts beneficial effects on CV and bone health. To this end we propose a randomized controlled trial to test this hypothesis in PHPT patients.

## Methods/design

### Study design, endpoints and safety

EPATH is a single-center, double-blind, placebo-controlled, randomized, parallel group trial. Patients with PHPT diagnosed according to the report of the 3rd International Workshop on Diagnosis of PHPT will be screened for inclusion into the study
[14]. Patients diagnosed with symptomatic/asymptomatic PHPT will be consented and screened for eligibility to participate in the EPATH trial. Overall 110 patients will be randomized to receive eplerenone or placebo in a 1:1 ratio (55 patients will receive eplerenone and 55 patients will receive placebo).

The design, conduction and reporting of the EPATH study adheres to the recommendations of the CONSORT Statement (
http://www.consort-statement.org/). The study will be performed in accordance with the Good Clinical Practice (GCP) guidelines and the Declaration of Helsinki. The study has been approved (N° 24–032 ex 11/12; EudraCT number: 2011-005683-21) by the Ethics Committee of the Medical University of Graz, Austria.

The primary endpoint of the study is to evaluate the efficacy of eplerenone relative to placebo to reduce PTH(1–84) concentration, measured by two different laboratory methods, in patients with PHPT. Secondary endpoints are the mean changes from baseline after 8-weeks with eplerenone versus placebo, in the following measurements: (1) 24-hour systolic and diastolic ambulatory blood pressure (ABP) levels; (2) biomakers of CVD; (3) biomarkers of bone metabolism: osteocalcin, β-crosslaps, bone alkaline phosphatase and tartrate-resistant acid phosphatase; (4) 24-h urinary albumin/protien excretion; and (5) echocardiographic parameters related to systolic and diastolic function as well as cardiac dimensions (i.e. left ventricular ejection fraction, E/E´ ratio, left ventricular end-diastolic/systolic pressure/volume/index and LV posterior wall thickness).

We decided to evaluate the effect of MR-blocker eplerenone on iPTH(1–84) - the primary outcome – and on CV and bone health – the secondary outcomes - after 8 weeks because (1) preliminary data from the Graz Endocrine Causes of Hypertension (GECOH) study suggest that MR-blockade with eplerenone might exert “rapid” effects on iPTH(1–84) levels
[15]; (2) eplerenone has been shown to significantly lower BP after a few days of treatment, indicating that this dose may be sufficient to impact on iPTH(1–84) levels

**Figure 1 F1:**
[figure not shown]
Flow chart for the EPATH trial.

Patients will be requested to be fasting and abstain from tea, coffee and smoking for overnight at least 12 hours before applying at the study outpatient. Intake of any drug should be avoided in the morning before blood collection. Investigations will be done in the morning (8:00 to 12:00). Extreme care will be taken to avoid haemolysis and prolonged stasis. Laboratory surveillance of serum electrolytes (potassium, sodium, magnesium and calcium) and renal function (serum creatinine and estimated glomerular filtration rate (GFR) according to the MDRD formula) is required at each study visit. Immediate suspension of the study drug eplerenone will be disposed for any measured serum potassium ≥ 5.5 mmol/L, and a down-titration of the study drug will be initiated for any measured serum potassium ≥ 5.0 mmol/L. Furthermore, the study drug will be discontinued in case of a rise of serum creatinine ≥ 3.0 mg/dL or GFR < 30 mL/min (or downtitration between GFR 30-49 mL/min), severe anaphylactic reactions following or intolerance due to eplerenone intake, requirement for an open-label use of eplerenone or potassium sparing diuretics, or formal withdrawal of the consent.

To minimise the risk of adverse events (e.g. hyperkalemia) patients with an eGFR ≤ 50 mL/min and/or a serum potassium > 5 mmol/L will be excluded from enrollment into the EPATH Study. Furthermore, the dose of 25 mg eplerenone once daily is comparably low and will be titrated to 50 mg once daily, if no adverse effects have been observed and if well tolerated.

If women of child-bearing age participate in the EPATH study, pregnancy will be ruled out at the beginning of the active participation before study enrolment. Further pregnancy tests will be performed monthly in our outpatients (spot urine test), and additionally as a self-test at home (after thorough education and instruction to perform test self-tests and after notification per telephone). Female participants of child-bearing age will be instructed to perform contraception throughout the active study period.

Because MR-blocker treatment is currently recommended in all patients with persisting symptoms (NYHA class II–IV) and an EF <35%, despite treatment with an ACE inhibitor (or an ARB) and a beta-blocker, special care was taken to avoid serious side effects such as hyperkalemia in PHPT patients by (1) excluding those participants from study participation, who are at higher risk of developing hyperkalemia; (2) a dose titration strategy; (3) monitoring of serum electrolytes and renal function at each study visit
[21].

Randomization will be done with assistance of the Institute of Medical Informatics, Statistics and Documentation of the Medical University of Graz (http://www.randomizer.at). The study staff and participants will be blinded to treatment assignment for the duration of the study.

Study medication of either eplerenone (Pfizer Corporation Austria, Vienna, Austria) or placebo will be packed in numbered pill boxes (identical in appearance and packages) according to both a computer generated randomization list and to international standards, respectively. This will be done by qualified staff at the pharmacy of the Medical University of Graz, which has extensive experience with placebo controlled trials.

### Setting

Eligible study participants will be recruited from the outpatient clinic of the Department of Internal Medicine, Division of Endocrinology and Metabolism and Division of Cardiology, Medical University of Graz, Austria. All baseline and follow-up visits will be conducted at the Department of Internal Medicine, Division of Endocrinology and Metabolism and Division of Cardiology and at the Center of Medical Research of the Medical University of Graz, Austria.

### Inclusion and exclusion criteria

Eligible patients will be men and women of at least 18 years of age with PHPT, who (1) do not meet criteria for surgical treatment; or (2) in whom surgery is recommended, but not performed because of patient and/or physician preference; or (3) perceived medical contraindications
[22].

Exclusion criteria include (1) 25(OH)D levels <20 ng/dl (50 nmol/liter); (2) estimated GFR (according to the MDRD formula) ≤ 50 ml/min; (3) serum potassium > 5.0 mEq/L (mmol/L) at baseline or > 5.5 mEq/L (mmol/L) during active study period; (4) side effects related to hypotension; (5) pregnancy or lactating women; (6) drug intake as part of another clinical study 4 weeks before enrolment into the EPATH study and/or during the active study period; (7) any disease with an estimated life expectancy below 1 year; (8) chemotherapy or radiation therapy during the study; (9) intolerance to eplerenone or any ingredient occurring in eplerenone; (10) severe acute or chronic liver diseases (Child-Pugh Class C); and (11) concurrent intake of potassium sparing drugs, e.g. diuretics (amiloride and triamterene) or CPY3A4-inhibitors and ongoing potassium supplementation.

### Measurements

#### Anthropometry

Weight and height will be measured wearing no shoes and light clothes and waist and hip ratio will be determined according to published recommendations.

#### Laboratory measurements

All blood samples will be centrifuged within 1 hour after sampling and will be measured at latest 4 hours after blood collection. Before analysis or freezing all samples will be kept at room temperature, except of the samples for determination of iPTH(1–84) (and plasma aldosterone), which will be kept at 4° Celsius. Remaining samples for long-term storage (whole blood, serum, plasma, urine and saliva samples) will be kept at −70° to 80° Celsius at the Biobank Institute of the Medical University of Graz.

Measurement of iPTH(1–84) (pg/mL) will be performed by electrochemiluminiscence immunoassay “ECLIA” (Elecsys immunoassay analyzer, Cobas®, Roche Diagnostics GmbH, Mannheim, Germany). The Elecsys assay for determining intact PTH employs a sandwich test principle in which a biotinylated monoclonal antibody reacts with the N-terminal fragment (1–37) and a monoclonal antibody labeled with a ruthenium complex reacts with the C-terminal fragment (38–84). The antibodies used in this assay are reactive with epitopes in the amino acid regions 26–32 and 37–42. Blood for iPTH(1–84) determination will be collected with standard EDTA plasma tubes and centrifuged within 5 to 10 minutes.

[Conversion factors of iPTH(1–84) are: pg/mL × 0.106 = pmol/L and pmol/L × 9.43 = pg/mL, respectively. Measuring range of the assay: 1.20 (=lower detection limit) to 5000 pg/mL (=maximum of the master curve); Reference range: 15–65 pg/mL, interassay coefficient of variation 3.0-6.5% for PTH 26.7-261 pg/mL).

PTH will be further determined using the electrochemiluminiscence LIAISON N-tact PTH immunoassay (DiaSorin Inc., Stillwater, MN, USA).

The measurements of further parameters (25(OH)D, osteocalcin, β-CrossLaps, bone alkaline phosphatase, tartrate-resistant acid phosphatase, osteoprotegerin, NT-pro-BNP) have been previously described in detail
[15,23].

All other laboratory measurements will be performed according to current routine laboratory methods at the Medical University of Graz.

Measurement of omics-based biomarkers will be performed by Liquid chromatography–mass spectrometry at the Clinical Institute of Medical and Chemical Laboratory Diagnostics, Medical University of Graz
[24].

#### Genetic investigations

Genetic analyses (e.g. PCR) will be performed in order to investigate the impact of e.g. polymorphisms of the calcium-sensing receptor or of the aldosterone synthase (CYP11B2) on PTH- and aldosterone secretion. Genome-wide association analyses will be performed - within the limits of a hypothesis testing strategy - in order to examine novel genes/loci implicated in the regulation of aldosterone and PTH synthesis in concert with larger studies. Genetic testing will be further initiated in suspicion of familial form of hyperparathyroidism. Emphasis will be placed upon the genes associated with familial hypocalciuric hypercalcemia (FHH), multiple endocrine neoplasia syndrome type I (MEN1), MEN2, and the hyperparathyroidism jaw-tumor syndrome.

#### Echocardiography

Comprehensive echocardiographic analysis of cardiac function and dimensions will be performed by experienced physicians on echocardiographic device (GE Vivid 3® Pro Echocardiography System, United Kingdom) according to current guidelines of the American Society of Echocardiography. Tissue Doppler indices will be recorded at the septal and lateral base of the mitral annulus.

#### 24-hour systolic/diastolic ambulatory blood pressure monitoring (ABPM)

Our stuff will be carefully trained to ensure the accuracy of the ABPM measurement. The ABPM measurements will be performed in accordance to the established protocols of the European Society of Hypertension and the American Association for Medical Instrumentation. Measurements of 24-hour ABP will be performed by a validated ABP monitor (Spacelabs 90217; Spacelabs Healthcare GmbH) and mean 24-hour systolic and diastolic ABP will be recorded. A minimum of 14 readings during the day and 7 readings overnight will be required for valid 24-hour ABPM.

#### Questionnaires

The validated Short Form 36 questionnaire (SF-36)12 will be used as a general estimate for qualtity of life. The Kansas City Cardiomyopathy Questionnaire is a 23-item, self-administered instrument, which will be used to quantify physical function, symptoms (frequency, severity and recent change), social function, self-efficacy and knowledge, and quality of life.

### Statistical methods

#### Sample size calculation

Sample size calculation for the primary endpoint iPTH(1–84) is based on (1) an observed effects of eplerenone treatment (and adrenalectomy) on iPTH(1–84) levels in a previously published study
[25]; (2) the proven significant association between (elevated) PTH levels on risk of fatal cardiovascular events in humans
[3]; and (3) data derived from patients, which have been managed at the outpatient clinic of the Division of Endocrinology and Metabolism at the Medical University of Graz, with primary hyperparathyroidism.

Based on the observational data from the GECOH study, MR-blockade (by eplerenone and spironolactone) in patients with primary aldosteronism was associated with an approximate 10.0 pg/mL decrease in PTH levels after a mean follow-up of 12 months
[25]. However, two patients at short-term follow-up of 4 weeks revealed a similar decrease of PTH levels with MR-blockade compared to long-term follow-up, indicating a rapid effect of MR-blockade on PTH levels. We are, however, aware that due to limited evidence regarding the effects of eplerenone in patients with PHPT, final conclusions cannot be drawn.

We further evaluated whether an increase of 10.0 pg/mL PTH is translated into a significant higher risk of CV mortality. In the LURIC study comprising 3.300 patients referred to coronary angiography the increment of 10 pg/mL PTH was significantly related to a 4% [Hazard Ratio (95% CI): 1.04 (1.03-1.06) p < 0.001] higher risk of cardiovascular death
[3]. We assumed an effect size of 10.0 pg/mL, assuring sufficient power to decrease PTH by eplerenone 25/50 mg once daily. Thus, for a two-sided alternative-hypothesis with an α of 0.05 and a power (1-β) of 80% we calculated a sample size of 51 study participants per group. To compensate for drop-outs during the study (estimated to around 10%) we plan to enrol 55 patients per group.

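### Enrolling 55 per group covers about 7% drop-out, slightly short of the stated allowance of around 10% on 51 evaluable patients per group (minor arithmetic error)

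*Protocol article*

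**What the plan says.** In the protocol article, the section *Sample size calculation* sets the error rates ("for a two-sided alternative-hypothesis with an α of 0.05 and a power (1-β) of 80"%) and the target difference ("We assumed an effect size of 10.0 pg/mL"). It reports the result as "we calculated a sample size of 51 study participants per group". The next sentence adds the drop-out allowance: "To compensate for drop-outs during the study (estimated to around 10%) we plan to enrol 55 patients per group".

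The section *Study design, endpoints and safety* carries the same enrolment figure: "Overall 110 patients will be randomized to receive eplerenone or placebo in a 1:1 ratio", with "55 patients will receive eplerenone and 55 patients will receive placebo". The total of 110 is therefore consistent throughout. The question is only whether 55 follows from 51 and a loss of around 10%.

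No standard deviation is printed. Among the sources for the calculation the section names "data derived from patients, which have been managed at the outpatient clinic of the Division of Endocrinology and Metabolism", but it does not give the variability taken from them.

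**The concern.** The required number, the expected loss and the enrolled number are all printed, so the step from 51 to 55 can be checked directly. It depends on no formula or software setting that the article leaves out. The sentence says that 55 compensates for the expected loss. If it does not, then 80% power, around 10% drop-out and 110 patients cannot all hold together as stated. What is at stake is the accuracy of the planning statement, and at most a small amount of power for the primary endpoint.

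**Working it through.** **Inputs** (all from *Sample size calculation*): required n = 51 per group; drop-out d = 10%, given as approximate; enrolled n = 55 per group; difference 10.0 pg/mL; two-sided alpha 0.05; power 80%.

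**Step 1. Try to reproduce 55.**
- Standard inflation, n/(1 - d): 51/0.90 = 56.7, rounded up to 57.
- Shortcut, n x (1 + d): 51 x 1.10 = 56.1, rounded up to 57. Rounding down would still give 56.
- The standard formula gives 55 at 7% loss (51/0.93 = 54.8) and 56 at 8% loss (51/0.92 = 55.4).

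Neither usual formula gives 55 from 51 at 10%.

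**Step 2. What 55 does cover.**
- Largest loss that leaves 51: 1 - 51/55 = 7.3%.
- Evaluable at 10% loss: 55 x 0.9 = 49.5 per group, so 49 or 50. In total this is 110 x 0.9 = 99, against 2 x 51 = 102 required: 3 patients short.
- Enrolment needed for 10% loss: 2 x 57 = 114, which is 4 more than 110.

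**Step 3. Effect on power.** With no standard deviation stated, it has to be back-calculated from n = 51. This is an assumption that takes the article's 51 and 80% as correct.

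Normal formula: SD = 10.0 x sqrt(51/2) / (1.960 + 0.842) = 18.02 pg/mL. Then power(n) = Phi(10.0 / (SD x sqrt(2/n)) - 1.960). The t-test equivalent uses a standardised difference of 0.560, that is SD = 17.85 pg/mL.

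If 51 was rounded up from just over 50, the t-test gives SD of about 17.67 pg/mL and slightly more power at each n.

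| Evaluable per group | 51 is exactly the 80% point (normal and t-test agree) | 51 rounded up from just over 50 (t-test) |
|---|---|---|
| 49 | 78.4% | 79.2% |
| 49.5 | 78.8% | 79.6% |
| 50 | 79.2% | 80.0% |
| 51 | 80.0% | 80.8% |

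So at 10% loss the power lies between 78.4% and 80.0%, about 79%.

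**Step 4. Possible offset from the analysis.** The *Outcomes* section plans an analysis of covariance adjusted for baseline. Suppose that 51 came from an unadjusted comparison of week-8 values, which the article does not say. Adjustment then multiplies the residual variance by 1 - r², where r is the correlation between baseline and week 8. The shortfall is made up when 1 - r² is at most 49.5/51 = 0.971, that is, when r is at least sqrt(0.029), about 0.17.

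**The case against.** The strongest reply is that the drop-out figure is explicitly approximate and is a planning guess. A gap of two patients per group is smaller than the uncertainty in that guess, and the power stays within 2 percentage points of 80% in every case above. If 51 was rounded up from just over 50, 50 evaluable patients per group still give 80%. The planned adjustment for baseline may also recover more than is lost. All of this stands as an argument about size. It does not make the sentence right: at the estimate that the sentence itself gives, 55 leaves fewer than 51, and approximate wording rescues it only if around 10% is read as no more than 7.3%.

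A reader might infer more than this, in three ways that the article does not support.

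- **That the trial is underpowered, or that 80% power is lost.** The shortfall is at most about 1.6 points. It is calculated from a standard deviation that was itself derived from the 51, so it cannot show that the true power is adequate or inadequate.
- **That withdrawals for potassium, renal function or intolerance come on top of the 10%.** The design section describes stopping study drug, and the exclusion criteria include a potassium limit during the active period. Neither says that these patients are additional to the estimated drop-outs. They may be the very patients being estimated, and no event rates are given.
- **That week-8 PTH will not be collected after study drug is stopped.** The article does not say so, and a condensed article may leave this to the full protocol.

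**Conclusion.** The point holds as a minor arithmetic error. At 10% loss, keeping 51 evaluable patients per group requires 57 enrolled. The 55 planned cover about 7% and would leave 49 to 50 per group. This part rests only on three printed numbers and needs no assumption.

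The effect on power, about 79% in place of 80%, is conditional on accepting the article's 51, because without a standard deviation neither the 51 nor the 80% can be verified from this document. Baseline adjustment might remove the shortfall altogether. Severity is low: the design, the analysis and the interpretation of the trial are unaffected.

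**What to change.** Keep 110 patients and correct the drop-out sentence. The preferred wording is that 55 per group allows for about 7% drop-out at the stated 80% power; it needs only the 51 and the 55. The alternative is to say that with 10% drop-out the power is about 79%. That version depends on the back-calculated standard deviation and should say so.

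The cost is one sentence and a slightly less favourable planning figure. No extra patients are needed, and the enrolment figures elsewhere in the article stay as they are. Raising enrolment to 57 per group would also make the numbers agree, but a shortfall of this size does not call for four more patients.
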